C-fibre subtypes are classified according to their response to an increase in electrical stimulation frequency to 2 Hz. This response, known as activity-dependent slowing of conduction velocity, is a characteristic feature of C-fibres in which conduction latency increases (i.e., slows) following repetitive stimulation. Using this method, five distinct populations of C-fibres can be identified: type 1A (“mechano-sensitive”) nociceptors, type 1B (“mechano-insensitive”) nociceptors, cold thermoreceptors, low-threshold mechanoreceptors, and cutaneous sympathetic efferent fibres [24,25].

There are two main reasons for distinguishing between a core and an extended recording protocol. The first relates to participant tolerability. Some individuals, particularly older participants, find prolonged recordings difficult due to musculoskeletal discomfort, difficulty keeping the limb still, challenges in following instructions, or urinary urgency. To minimise discomfort, participants are seated in a supportive chair with pillows to cushion pressure points, and are offered comfort breaks at the start of the recording. The second reason concerns recording stability. C-fibre signals may be lost during longer sessions because of small movements of the electrode or limb, or loss of contact during natural stimulation. As a result, extended recordings cannot always be completed. To prevent ascertainment bias, data from the extended protocol will therefore be treated as secondary or exploratory outcomes.

Microneurography measurements will include measures of:

Axonal properties

i. Baseline conduction velocity.ii. Degree of activity-dependant slowing to several stimulation frequencies (e.g., 0.25 Hz to 2 Hz)iii. Action potential morphology analysis of the extracellular recorded action potentialsiv. Threshold responses to thermal and mechanical stimulation

Nociceptor excitability

i. Spontaneous activityii. Double or multiple spikesiii. Thermal and mechanical sensitisation defined as prolonged ongoing discharges outlasting stimulus duration or lowered thresholds in response to thermal and mechanical stimulation.

Axonal excitability (across all C-fibre types)

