#### Study hypotheses.

The primary hypothesis is that participants with neuropathic pain will exhibit altered axonal properties and excitability compared to those without neuropathic pain.

Secondary hypotheses we will test are:

1) Somatosensory subgroups will match nociceptor properties. The planned outcomes are comparisons between neurophysiological and sensory phenotype variables, for example, mechanical hyperalgesia sensory profile will show lowered neurophysiological threshold to mechanical stimulation.2) Genetic variants will confer a unique nociceptive axonal profile and excitability signature. The planned outcome is the comparison of nociceptor fibre excitability and axonal properties between those participants with and without genetic variants.

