#### Primary outcome comparisons.

Comparison of mean values and distributions of axonal excitability and axonal property measures at participant level for individual nociceptive fibres (for example, spontaneous activity, multiple spikes, mechanical and thermal sensitisation, conduction velocity, and activity-dependent slowing).

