#### Risk of bias and mitigation.

Potential sources of bias include misclassification of fibre type, sampling bias, outcome reporting bias and confounding.

Fibre classification bias will be minimised using pre-specified, reproducible criteria based on activity-dependent slowing of conduction velocity. Sampling bias will be reduced by recording from multiple receptive fields per participant and using mixed-effects models to account for within-participant variability. Confounders will be adjusted for in regression models. The protocol and statistical analysis plan will be pre-specified and published to minimise outcome reporting bias.

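### Slowing at 2 Hz decides which fibres count as nociceptors and is also a primary outcome in those fibres, so that one comparison is conditioned on its own outcome

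*Protocol article*

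**What the plan says.** All references are to the protocol article.

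- **Classifier (Microneurography).** "C-fibre subtypes are classified according to their response to an increase in electrical stimulation frequency to 2 Hz". The section calls this response activity-dependent slowing and continues: "Using this method, five distinct populations of C-fibres can be identified: type 1A (“mechano-sensitive”) nociceptors, type 1B (“mechano-insensitive”) nociceptors, cold thermoreceptors", followed by low-threshold mechanoreceptors and sympathetic efferents. The rule therefore sets nociceptor status as well as the split between types 1A and 1B.
- **Measurement (Microneurography).** The listed axonal properties include "Degree of activity-dependant slowing to several stimulation frequencies (e.g., 0.25 Hz to 2 Hz". The 2 Hz block belongs to the core protocol that every C-fibre undergoes. Natural stimulation belongs to the optional extended protocol, whose data are secondary or exploratory.
- **Primary outcome (Primary outcome comparisons).** "Comparison of mean values and distributions of axonal excitability and axonal property measures at participant level for individual nociceptive fibres", with the examples "for example, spontaneous activity, multiple spikes, mechanical and thermal sensitisation, conduction velocity, and activity-dependent slowing".
- **Hypothesis (Study hypotheses).** "participants with neuropathic pain will exhibit altered axonal properties and excitability compared to those without neuropathic pain".
- **Protection claimed (Risk of bias and mitigation).** "Fibre classification bias will be minimised using pre-specified, reproducible criteria based on activity-dependent slowing of conduction velocity".

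**The concern.** The same 2 Hz block supplies both the rule that admits a fibre to the comparison and one of the quantities compared. If the primary hypothesis is true for slowing, fibres near a class boundary change class because of the effect under study. Each class is then truncated on its own outcome. Part of a real effect appears as a change in how many fibres fall in each class, and the difference in mean slowing among fibres of a given label usually shrinks.

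At stake is the reading of a small or null slowing result. With the comparison as described, such a result could mean that slowing is unchanged, or that part of the change has been absorbed by the labels. Averaging within participants and a participant random effect, both in Planned primary analysis, deal with clustering of fibres. They do not deal with this selection.

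**Working it through.** **No plan figure to reproduce.** The article gives no slowing cut-off, standard deviation, class share or expected effect. The overlap follows from setting the Microneurography and Primary outcome comparisons sections side by side. Its size can only be illustrated.

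**Model A: two adjacent fibre types, compared separately.** Assumptions: slowing is normal with SD 1 in each type, means are 3 or 4 SD apart, the cut is midway (c = 1.5 or 2), the mix is 2:1, and only the lower type shifts upward by d. The difference seen among lower-type fibres that keep their label is

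d − φ(c−d)/Φ(c−d) + φ(c)/Φ(c).

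- c = 1.5, d = 0.5: 0.5 − 0.2420/0.8413 + 0.1295/0.9332 = 0.351, which is 70% of d.
- c = 1.5, d = 1.0: 1.0 − 0.3521/0.6915 + 0.1295/0.9332 = 0.630, which is 63%.
- c = 2, d = 0.5: 0.5 − 0.1295/0.9332 + 0.0540/0.9772 = 0.416, which is 83%.
- c = 2, d = 1.0: 1.0 − 0.2420/0.8413 + 0.0540/0.9772 = 0.768, which is 77%.

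The share of the lower type that is relabelled, 1 − Φ(c−d), is 7–31% after the shift, against 2–7% before it. The upper type, truly unchanged, shows a false shift of −0.12 to −0.30 SD. Counting upper-type fibres mislabelled into the lower class changes 63–83% only slightly, to 61–83%. If both types in this model are pooled, relabelling between them loses nothing.

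**Model B: three classes, so that the nociceptor boundary is included.** Assumptions: shares of 20% non-nociceptor, 50% type 1A and 30% type 1B, in that order on the slowing scale; SD 1; equal spacing s; cuts at the midpoints; every nociceptor in the pain group shifted by D. Share of D that remains (simulation, 1,000,000 fibres per group; exact integration agrees to within about 1–2 percentage points):

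| s (SD) | D (SD) | Within 1A | Within 1B | Pooled nociceptors |
|---|---|---|---|---|
| 2 | +0.5 | 19% | 35% | 71% |
| 2 | −0.5 | 15% | 34% | 57% |
| 3 | +0.5 | 45% | 44% | 82% |
| 3 | −0.5 | 36% | 52% | 67% |
| 4 | +0.5 | 71% | 64% | 93% |
| 4 | −0.5 | 63% | 73% | 80% |
| 6 | +0.5 | 96% | 93% | about 100% |
| 6 | −0.5 | 95% | 96% | 97% |

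At s = 3 and D = +0.5, true 1A fibres labelled 1B rise from 6.7% to 15.9%, and the share of all fibres called 1B rises from 31% to 37%. This is the part of the effect that moves into the class mix.

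**Reading the two models together at 3–4 SD.** Pooled nociceptors keep 67–93% of a 0.5 SD shift. Separate types keep 44–71% for an upward 0.5 SD shift of all nociceptors (Model B) and 63–83% if only one type shifts (Model A). The lowest values at this spacing are 36% (within 1A, D = −0.5) and 37% (within 1B, D = +1.0).

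**Effect of dropping the selection.** Over all C-fibres the mean moves by D × 0.8 in Model B, because 20% of fibres are unshifted; for D = 0.5 that is 0.40 SD. Nothing is lost to labelling: dividing by 0.8 recovers 98–103% of D in the simulation. But the comparison responds to fibre mix. At s = 3, if 5 percentage points of fibres truly were 1B instead of 1A, the mean would move by 0.05 × 3 = 0.15 SD with no change in any fibre's slowing.

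**The case against.** **The separate-type figures describe an analysis the article does not state.** It speaks of nociceptive fibres, and 1A and 1B are both nociceptors, so a fibre crossing between them stays in a pooled set. This stands. A reader might infer that the planned primary analysis loses the larger amounts shown for separate types; the text does not support that. With pooling, only the boundary between nociceptors and other fibres matters. That boundary also rests on slowing, so the loss is smaller but not zero.

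**The separation is assumed.** The article calls the populations distinct, and the criteria it cites may use the response pattern and not one threshold. This also stands. At 6 SD almost nothing is lost. Unseen cut-offs can make the effect small, but they leave classifier and outcome drawn from the same response.

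**Other outcomes.** A reader might infer that all primary measures are biased in this way. They are not selected on themselves; they are touched only through relabelled fibres. The recovery cycle is defined over every C-fibre type.

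**Obvious remedies have their own faults.** Replacing the nociceptor comparison with one over all C-fibres would mix slowing with fibre composition. Classifying by mechanical response would overlap with mechanical sensitisation, another listed primary measure, and would rely on optional data. Both points stand and limit the fix.

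**The bias statement concerns consistent labelling.** That is a fair reading, and consistent labels are worth having. They give the slowing outcome no protection, and the sentence does not say so.

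**Conclusion.** The overlap is explicit in the text: slowing at 2 Hz defines the fibres in which slowing is a primary outcome. The direction follows from truncation: if pain status alters slowing, part of the change can pass into the class mix and the within-class difference is usually attenuated.

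The size is conditional. It rests on assumed normal classes with unit SD, midpoint cuts and the shares stated above. At 3–4 SD separation the loss ranges from modest to about a third of a 0.5 SD shift if nociceptors are pooled, and is larger if 1A and 1B are analysed separately. It is close to nothing at about 6 SD. The article does not say which of the two analyses is intended.

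The stronger conclusion that the slowing comparison is invalid and should be dropped is not supported. The point is worth correcting before analysis because, as described, a null slowing result would be hard to interpret.

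**What to change.** Keep the planned comparison in nociceptive fibres and make these changes:

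1. State whether types 1A and 1B are pooled or analysed separately for slowing.
2. Report the proportions of all fibre classes, including 1A and 1B, by pain group as an outcome.
3. Add a supporting comparison of the full slowing distribution over all C-fibres identified at 0.25 Hz, without selection on class. Read it together with item 2, because a difference in fibre mix can also move it.
4. Qualify Risk of bias and mitigation: slowing-based criteria make labels consistent but do not protect the slowing outcome itself.
5. Label any reclassification by mechanical response as exploratory only.

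The cost is a few sentences and a little extra analysis. Items 2 and 3 use core-protocol data and need no further recording. The drawback is that the added comparison is less specific to nociceptors, so it supports the planned analysis and does not replace it.

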**Strengths and limitations of this study:**

The study uses microneurography, the only technique that directly records from human nociceptors in vivo, enabling detailed mechanistic assessment of C-fibre function. A deep phenotyping framework, including quantitative sensory testing, skin biopsy, nerve conduction studies, and genetic analysis, allows multidomain integration of clinical, neurophysiological, and molecular data. Classification of C-fibre subtypes using activity-dependent slowing provides a reproducible method to distinguish functional nociceptor populations. Extended microneurography protocols may not be feasible for all participants due to tolerability or signal instability, potentially reducing completeness of some secondary measures. As an observational study, causal inference is limited, and confounding will require careful adjustment despite prespecified statistical analyses.

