### Specialised investigations

#### Microneurography.

Microneurography records single-unit activity from peripheral sensory nerves in awake participants by inserting a microelectrode into a peripheral nerve [54]. We typically use the superficial peroneal nerve on the dorsum of the foot because it is superficial, purely sensory, anatomically relevant to distal symmetrical polyneuropathy, and generally well tolerated. It is also the most distal nerve available, which provides an advantage for length-dependent (‘dying-back’) neuropathies that show a distal-to-proximal gradient. In older participants (>70 years) or those with severe neuropathy where the superficial peroneal nerve is denervated or inaccessible, alternative sites (superficial radial nerve or more proximal peroneal sites) will be used.

C-fibres are characterised by the phenomenon of activity-dependent slowing of conduction velocity in response to repetitive transcutaneous electrical stimuli, and natural stimulation in a series of experiments [24].

The core protocol will consist of:

Identification of C-fibres at 0.25 Hz stimulation. After identification, stimulation is paused for three minutes to allow baseline recovery, followed by six minutes at 0.25 Hz. The rate is then increased to 2 Hz for three minutes and followed by a further six minutes at 0.25 Hz. The pause and 0.25 Hz blocks may be adjusted for participant tolerability, but the 2 Hz block will not be shortened.

Where possible this will be followed by the extended protocol.

Stimulation at 0.125 Hz, 0.25 Hz, 0.5 Hz and 1 Hz for at least two minutes at each frequency.Paired-pulse testing to assess recovery cycles by delivering a test stimulus at progressively shorter intervals after a conditioning stimulus.Mechanical and thermal natural stimulation of the receptive field using von Frey hairs and thermal probes (40°C, 45°C, 48°C and 20°C) to determine transduction thresholds and sensitisation to mechanical and thermal stimulation.

We aim to record from up to three independent receptive fields per participant, but a single stable recording suffices for inclusion. All C-fibres will undergo the core protocol; the extended protocol is optional and recorded whenever feasible.

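### Ranking extended-protocol data as secondary does not prevent ascertainment bias: selective completion stays in every comparison of those data, and the primary list still names extended-only measures

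*Protocol article*

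**What the plan says.** The Microneurography section of the protocol article splits recording into two stages. The core protocol is electrical only: blocks at 0.25 Hz and 2 Hz, with a pause. The extended protocol adds further frequencies, paired pulses, and this step: "Mechanical and thermal natural stimulation of the receptive field using von Frey hairs and thermal probes". On who receives which stage it says: "All C-fibres will undergo the core protocol; the extended protocol is optional and recorded whenever feasible".

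The section gives two reasons for the split. One is tolerability: "Some individuals, particularly older participants, find prolonged recordings difficult due to musculoskeletal discomfort". The other is stability: "C-fibre signals may be lost during longer sessions because of small movements of the electrode or limb, or loss of contact during natural stimulation". It then concludes: "To prevent ascertainment bias, data from the extended protocol will therefore be treated as secondary or exploratory outcomes".

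Four other sections bear on this:

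- Study hypotheses illustrates secondary hypothesis 1 by predicting that a "mechanical hyperalgesia sensory profile will show lowered neurophysiological threshold to mechanical stimulation".
- Secondary analyses compares microneurography variables across the three sensory groups by Kruskal–Wallis or one-way ANOVA, and names no covariates.
- Primary outcome comparisons includes mechanical and thermal sensitisation among its examples of primary measures.
- Strengths and limitations describes the effect of incomplete extended recordings as "potentially reducing completeness of some secondary measures".

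**The concern.** The article recognises that extended recordings are obtained selectively and offers the outcome's rank as the safeguard. Rank governs how much weight a result carries. It does not change which participants and fibres supply the data. A threshold comparison among those who completed the extended stage carries the same selection whether it is called primary, secondary or exploratory.

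Two things are at stake. The mechanical-threshold prediction under secondary hypothesis 1 would be judged on a selected subset, under a stated protection that does not reach it. The primary comparison may also draw on the same selected data through the sensitisation measures.

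**Working it through.** The plan gives no completion rate and no figure for this bias, so there is nothing to reproduce. The check traces each measure to its stage and then illustrates what selective completion can do.

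**1. Where each measure comes from, and how it is used**

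| Measure | Stage that supplies it | Use in the plan |
|---|---|---|
| Conduction velocity, slowing at 2 Hz | Core | Primary; also available for hypothesis 1 |
| Mechanical threshold | Extended only | Worked example of hypothesis 1 |
| Mechanical and thermal sensitisation | Extended only | Named under Primary outcome comparisons |

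Activity-dependent slowing in the core protocol assigns a fibre to a class. It gives no mechanical threshold, so the worked example depends wholly on extended data. The sensitisation row contradicts the statement that extended data are secondary or exploratory.

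**2. Whether another section deals with selective completion**

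Risk of bias and mitigation relies on several receptive fields per participant, mixed models for within-participant variability, and regression adjustment for confounders. None of these is directed at who completes the extended stage. Strengths and limitations speaks of completeness, not selection.

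**3. Illustration (all selection inputs are assumptions)**

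The threshold T is in SD units. The mechanical hyperalgesia share is set at 23%, between the 21.2% and 25.0% in Sample size justification. The model is logit P(complete) = b·T + s·(hyperalgesia group), with 2,000,000 draws. Differences are hyperalgesia minus the rest.

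| True difference | Selection | Difference among completers |
|---|---|---|
| 0 | none | 0.00 |
| 0 | b = 0.5 or 1 in both groups, s = 0 | 0.00 |
| 0 | b = 0.5 in hyperalgesia only | +0.24 |
| 0 | b = 0.5 in the rest only | -0.23 |
| 0 | b = 0.5, s = -1 | +0.11 |
| 0 | b = 1, s = -1 / s = -2 | +0.17 / +0.33 |
| -0.50 | none | -0.50 |
| -0.50 | b = 0.5 / b = 1, s = 0 | -0.47 / -0.41 |
| -0.50 | b = 1, s = -1 / s = -2 | -0.24 / -0.11 |

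A second set of runs (200,000 records per setting) assumed 60% completion and a true difference of -0.50.

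- Completion falling with severity (log-odds 0.8 to 1.2 per SD, severity–threshold correlation 0.4 to 0.6) gave -0.47, -0.43 and -0.41. Weighting by completion probability returned -0.50, -0.49 and -0.50.
- Loss of the most sensitive fibres gave -0.44, which weighting on observed data cannot fully repair.
- Both mechanisms together gave -0.52, because they offset.

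**4. Scale against sampling error**

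- Expected participants with a recording, from the plan's success rates: 124 × 0.60 + 148 × 0.80 = 74.4 + 118.4 = 192.8.
- With mechanical hyperalgesia: 74.4 × 0.25 + 118.4 × 0.212 = 18.6 + 25.1 = 43.7. This assumes that the pilot cluster shares apply to everyone recorded.
- At an assumed 60% completion: about 26 against 89.
- Standard error of the difference: √(1/26 + 1/89) ≈ 0.22 SD.
- The severity-driven shifts of 0.03 to 0.09 SD are therefore 0.03/0.22 ≈ 0.1 to 0.09/0.22 ≈ 0.4 of one standard error.

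**The case against.** The strongest defence is that the sentence explains why there are two stages. Read in that setting, demoting outcomes that cannot always be obtained is a legitimate way to keep selective completion out of the primary comparison, and the article nowhere says that comparisons within the extended data are free of selection. That reading is fair, and it is why the remedy is a rewording and not a redesign. It is not a full answer, because the primary list still contains extended-only measures.

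Four stronger readings are tempting, and the documents do not support them.

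- **Loss follows neuropathy severity or fibre sensitivity.** The article names age, discomfort, keeping still, following instructions, urinary urgency, movement and contact loss. Links to severity or sensitivity are plausible inferences that it does not state.
- **The threshold contrast will be biased by a known amount.** The inputs are assumed. The severity-driven results are small against the standard error, one combination nearly cancels, and the larger shifts need differential completion that the documents do not describe.
- **Secondary hypothesis 1 as a whole is compromised.** The mechanical threshold is offered only as an example. Core measures can be compared across sensory groups without this problem.
- **The plan has no handling of incomplete extended data.** Such detail commonly sits in a statistical analysis plan, which is not shown here. The finding is that the safeguard the article does state cannot do what it is said to do.

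**Conclusion.** The point holds in a limited form. Treating extended data as secondary or exploratory can at best shield the primary comparison. As written it does not achieve that, because the Microneurography section and Primary outcome comparisons disagree about the rank of mechanical and thermal sensitisation and must be reconciled. Selection remains in comparisons of extended data, including the mechanical-threshold example.

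Neither the size nor the direction of any bias can be determined from the documents. With no true difference, bias vanishes if completion is unrelated to threshold or related to it identically in all groups. With a true difference of -0.50 SD, an identical relation still shrank it to -0.47 or -0.41 in the illustration. The tracing of measures to stages rests on the article's text alone. Every bias figure rests on assumed completion rates and slopes. This is a correction to a stated safeguard and to reporting, and it does not show that the hypothesis-1 result will be wrong.

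**What to change.** 1. Reword the sentence in the Microneurography section. It should say that the demotion is meant to limit the effect of selective completion on the primary comparison, and that comparisons within extended data remain open to it.
2. Reconcile that section with Primary outcome comparisons, so that each extended-only measure has one stated rank.
3. Tabulate extended-protocol completion by sensory group and pain status, with the reason for stopping where recorded.
4. Compare completers with non-completers on core measures, age and neuropathy severity.
5. Beside each completers-only estimate from extended data, report a sensitivity analysis weighted or adjusted for predictors of completion: core measures, age, severity, pain status and medication. If the two differ materially, interpret the hypothesis-1 threshold results with caution. A rule that withholds support whenever they differ would be too strict, because they will differ by chance in groups of this size.

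The cost is one table, one comparison and one extra model, mostly from data already collected. A reason-for-stopping field may be new. Recruitment runs from February 2022 to September 2029, so it can be captured from now on, but past recordings may lack it. Weighted intervals will be slightly wider, and loss driven by the threshold itself cannot be fully corrected.
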